### Settings and Participants

Eligible government-funded primary schools located within a large city in North West England will be invited to participate in the study via email and telephone. Eligible schools are required to be located within an area ranked within the most deprived tertile for the English population, as measured by the 2015 English indices of deprivation index (Ministry of Housing Communities Local Government, 2018). Representatives from eligible schools will subsequently be invited to an information meeting with the research team, where they will be given an in-depth overview of the project. Signed consent will be obtained from headteachers for recruitment, data collection and potential delivery of PE by the research team. Eligible children from year 1 classes will then be invited to participate in the study via a parent/carer and child invitation pack, including information sheets, consent forms, parent and child characteristics questionnaire, child medical information form, and child assent form. Children that are not able to participate in PE (e.g., due to medical conditions) or those with profound learning disabilities and formally recognized special educational needs (e.g., behavioral issues, speech and language impairment) will be excluded from assessments and data analysis. Children that do not return parent consent forms will be exempt from the research, but able to participate in PE lessons.

### Blinding and Randomization

For practical reasons, it will not be possible to blind the researchers, teachers, and coaches to group allocation. Following collection of headteacher consent, randomization will take place at the school (cluster) level. Schools will then be matched based on the number of students enrolled and level of deprivation identified using the school postcode (Ministry of Housing Communities Local Government, 2018). Following this, schools will be randomly allocated to an intervention condition or control group using a computer-based random number producing algorithm by an independent researcher not associated with the study. This method ensures that schools had an equal chance of allocation to each group.

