**Methods:**

SAMPLE-PE will be evaluated through a cluster-randomized controlled trial targeting 5–6 year old children from schools located in areas of high deprivation in Merseyside, North-West England. Schools will be randomly allocated to one of three conditions: *Linear Pedagogy*, *Non-linear Pedagogy*, or Control. Non-linear and Linear Pedagogy intervention primary schools will receive a PE curriculum delivered by trained coaches over 15 weeks, while control schools will follow their usual practice. Data will be collected at baseline (T0), immediately post-intervention (T1), and 6 months after the intervention has finished (T2). Children’s movement competence is the primary outcome in this trial. Secondary outcomes include physical activity, perceived competence, motivation, executive functions, and self-regulation. An extensive process evaluation will also examine implementation factors such as intervention context, reach, dose, fidelity and acceptability.

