#### Primary Outcome

##### Movement competence

Movement competence will be assessed through a battery of assessments to examine both technical movement proficiency and movement creativity across different domains (locomotor, object-control, and stability skills). All movement competence assessments will take place during school hours within the school hall or playground and video-recorded for later analysis. Trained research assistants who have established acceptable agreement (80%) in terms of intra-rater and inter-rater reliability with pre-coded videos, will complete analysis of video recordings.

Movement proficiency (technique) will be assessed using the Test of Gross Motor Development-3 (TGMD-3; Maeng et al., 2016) and the Test of Stability Skills (Rudd et al., 2015). Specifically, six locomotor (run, gallop, hop, skip, horizontal jump, slide) and seven object-control (two-hand strike, one-hand strike, one-hand dribble, two-hand catch, kick, overhand throw, underhand throw) skills will be assessed using the TGMD-3 (∼30 min to complete). Proficiency at stability skills will be assessed using the three tasks (log roll, rock, back support) from within the Test of Stability Skills (∼15 min to complete). The psychometric quality of these assessments has been well-established (Rudd et al., 2015; Maeng et al., 2016). Participants will receive a verbal explanation and single demonstration from the assessor and are then given one practice attempt before undertaking two trials of each skill.

Movement creativity will be assessed using the Divergent Movement Ability Assessment (Cleland, 1990), which requires children to complete three stations, a stability skill station, a locomotor skill station and object control skill station (∼15 min to complete). In the stability station, children are asked to make as many shapes on or around the bench as they can. In the locomotor station, children are challenged to find as many different ways to move around the obstacle course as possible. Finally, in the object-control skill station, children will be asked to play with a large ball in a designated area, showing all the different skills and ways that they can play with the ball. For every station, children will complete two 90 s trials, during which, every 30 s the child will get a predefined prompt from the research assistant to support and encourage the child.

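### The blinding statement exempts no one, so arm-linked expectation bias can enter the later video scoring of the primary outcome, a step that could be masked

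*Protocol article*

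**What the plan says.** Under Blinding and Randomization, the article states that for unspecified practical reasons "it will not be possible to blind the researchers, teachers, and coaches to group allocation". No group of researchers is set apart as masked.

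The Abstract says that "Children’s movement competence is the primary outcome in this trial". Under Primary Outcome, Movement competence, this comprises the TGMD-3 and the Test of Stability Skills (technique) and the Divergent Movement Ability Assessment (creativity). All of these take place "within the school hall or playground and video-recorded for later analysis". Research assistants "who have established acceptable agreement (80%) in terms of intra-rater and inter-rater reliability with pre-coded videos" then "will complete analysis of video recordings". That agreement threshold is the only safeguard given for scoring. Masking of coders is not mentioned.

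The Hypotheses section predicts that both interventions will exceed usual practice on movement competence, and that Non-linear will exceed Linear on creativity but fall below it on technical proficiency.

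**The concern.** Filming separates the moment of performance from the moment of judgement. Staff in the school hall will probably know the arm. A coder working later from a recording need not. The blanket statement gives up that advantage for the primary outcome without giving a reason that fits the scoring step.

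The outcome is exposed in three ways:
- The scores are human judgements, and a coder who knows the arm also knows the result the team expects.
- The research team trains the coaches and meets them weekly (Training Coaches for Intervention Delivery), and researchers observe lessons and code lesson videos (Process Evaluation). Nothing in the article separates these roles from outcome scoring.
- A scoring lean tied to arm looks exactly like a treatment effect. The mixed models and covariates under Data Analysis cannot separate the two.

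**Working it through.** The plan gives no figure for scoring bias, so the main check is textual. The arithmetic in step 4 is illustrative.

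**1. Does the stated reason reach the scoring step?** Blinding and Randomization rules out blinding of researchers. Movement competence has the tests "video-recorded for later analysis". Coaches know what they teach, and a field tester stands in a school whose programme may be obvious. Neither fact bears on a person scoring a clip later.

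**2. Does the agreement criterion cover it?** No. It is met on pre-coded reference videos and shows that coders apply the criteria consistently. Coders can pass it and still lean by arm on trial clips.

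**3. Which knowledge matters, arm or time point?** Write a score as true value + scoring bias + random error.
- If the bias depends on arm, the expected contrast with control is δ + (β_arm − β_control). The bias stays in the estimate.
- If it depends only on time point, with leniency λ0 at T0 and λ1 at T1, each arm's gain shifts by λ1 − λ0. The between-arm difference in gains shifts by (λ1 − λ0) − (λ1 − λ0) = 0.

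Knowing the time point therefore distorts the trial's comparison mainly when the arm is known as well.

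**4. Illustration of size.** Inputs from Sample Size and Statistical Power: d = 0.4, class size 20, ICC 0.16, α = 0.05, 218 children before and 314 after allowance for dropout. Assumptions: two-sided normal test, outcome SD 1, true effect 0, and b, the difference in scoring bias between two arms in SD units.

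Design effect: 1 + (20 − 1) × 0.16 = 4.04, as the article has it.

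Standard error: SE = √[4.04 × (1/n1 + 1/n2)].
- 314 children in equal thirds (104.67 per arm): √(4.04 × 2/104.67) = 0.278.
- 218 children in equal thirds (72.67 per arm): √(4.04 × 2/72.67) = 0.333.
- One intervention arm with a quarter of the children against a control arm with half (the article heads the control section with 6 of the 12 schools) gives the same values, because 4 + 2 = 3 + 3.

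False-positive rate: 1 − Φ(1.96 − b/SE) + Φ(−1.96 − b/SE).

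| b (SD, assumed) | b as share of d = 0.4 | Rate, N = 314 | Rate, N = 218 |
|---|---|---|---|
| 0 | 0% | 5.0% | 5.0% |
| 0.05 | 12.5% | 5.4% | 5.3% |
| 0.1 | 25% | 6.5% | 6.0% |
| 0.2 | 50% | 11.1% | 9.2% |
| 0.3 | 75% | 19.1% | 14.7% |
| 0.4 | 100% | 30.2% | 22.4% |

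The table shows what a given bias would do. It is not evidence that bias of any size exists.

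**The case against.** - **The article does not say that the coders know the arm.** The blinding sentence names researchers; the scoring sentence names research assistants. A reader might infer that unmasked coding is stated and bias therefore established. It is not: the coders' knowledge is an inference from a statement that exempts nobody. This stands, and it limits the point to bias that can enter.
- **Operational detail belongs elsewhere.** Clip labelling and scoring rotas may be in the full protocol, and a SPIRIT checklist is cited as a supplement that is not shown. Their absence is no finding. The finding is what the article does state: if another document masks the coders, the published sentence is too broad and needs the same correction.
- **Time-point knowledge is not a second bias of equal weight.** A reader might take it as one. Step 3 shows that on its own it largely cancels between arms. Masking it is also only partly achievable, as children are a year older at T2.
- **Masked clips would not clear the primary outcome of bias.** In the proficiency tests, "Participants will receive a verbal explanation and single demonstration from the assessor". In the creativity test a research assistant prompts the child every 30 seconds. Unblinded staff can influence performance before any coding. With 12 schools, a hall or a uniform may also identify the school. All of this stands; the gain is confined to the scoring step.
- **Staffing.** The number of coders is not given. Testing takes about 30 + 15 + 15 = 60 minutes per child at each time point, so 314 children at three time points imply up to 314 × 3 × 1 h = 942 hours of footage before dropout. A strict rule against any overlap of roles may be hard to staff. This stands, and the fix makes that element conditional.

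**Conclusion.** The concern holds as a fault in the blinding statement. It rules out masking for researchers in general, while the primary outcome is scored in a deferred step to which the stated reason does not apply. As written, the plan leaves a judgement-based primary outcome with published directional hypotheses open to arm-linked scoring bias, which neither the agreement criterion nor the analysis can remove.

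The size and direction of any bias are unknown. The 0.1 to 0.2 SD range (25% to 50% of the planned effect; false-positive rate 6.5% to 11.1% at 314 children) is an assumption chosen for illustration. A reader might conclude that results will be biased towards the hypotheses, or that masked coding would remove most bias from the primary outcome. The document supports neither reading. The change should be made; confidence is high about the wording and lower about what the coders actually know.

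**What to change.** In Blinding and Randomization, limit the statement that blinding is not possible to teachers, coaches and on-site or delivery staff. Then state that:
- video coders are masked to arm;
- clips carry random identifiers, with school labels and dates removed;
- clips from T0, T1 and T2 are mixed in random order, as a secondary aid;
- where the existing team allows, no coder scores a school where they trained coaches, observed lessons or collected data;
- residual unmasking, such as a recognised setting or uniform, is recorded and reported.

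The Design section places the last data collection in January to February 2019, before the article appeared. The remedy needs no return to schools: recordings can be scored, or re-scored, in this way provided they have been kept.

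The cost is file handling and scheduling. The role-separation rule may strain a small team. Masking will be imperfect where settings are recognisable, and live demonstration and prompting by unblinded assessors are left untouched and should be acknowledged as a remaining limitation.

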### Intervention

#### Overview

SAMPLE-PE aims to explore the efficacy of two PE pedagogies (Non-linear Pedagogy and Linear Pedagogy), delivered through a 15-week PE curriculum in primary schools situated in areas of high deprivation. Each school being assigned to one of three conditions: Non-linear Pedagogy PE intervention, Linear Pedagogy PE intervention or control group (standard PE curriculum). All groups will have the same dose of PE (i.e., 2 × 60 min weekly PE lessons, for 15 weeks).

The SAMPLE-PE intervention curriculum for both the Linear Pedagogy and Non-linear Pedagogy arms will consists of 3, 5-week phases of lesson delivery commencing 2 weeks after baseline assessments. The first phase focuses on dance, the second on gymnastics and the final phase on ball sports. Each phase has its own scheme of work, which includes five lesson objectives, each taught over a two lesson period, and delivered in school during existing PE curriculum time. The lesson objectives are aligned to the aims of the English national curriculum (Department for Education, 2013) and are identical in both Linear and Non-linear Pedagogy schemes of work, but the content was differentiated by pedagogical approach in an effort to support the development of the lesson plans (described in detail below). Lessons will be delivered by trained coaches, with 45 min of on-task teaching time of the total 60 min overall lesson time, culminating in a total of 30 PE lessons.

#### Training Coaches for Intervention Delivery

The present study is both an efficacy and an effectiveness trial. Given that there is evidence that some generalist primary school teachers lack the confidence and competence to effectively teach PE (Morgan and Hansen, 2008), coaches will be recruited to deliver the Linear and Non-linear Pedagogy PE interventions. This approach also corresponds with current practice in primary PE in England, as the majority of primary schools currently source external providers who employ sports coaches to deliver PE (Griggs, 2016). Sport coaches will be recruited through advertisements aimed at postgraduate and undergraduate students undertaking Sports Coaching or PE courses or via the university’s in-house sports coaching provider. Applicants will be shortlisted if they have a level 2 coaching qualification in any sport, meaning that they can independently plan, prepare and deliver sessions and they have basic emergency first aid, safeguarding and protecting children certificates. Further, it is desirable that coaches will have at least 1-year’s coaching and/or PE teaching experience in a primary school or sports club setting. Recruited coaches will then be invited to attend a bespoke 5-week training programme. This training aims to develop the coaches’ knowledge and skills to deliver either a Linear (operationally through Direct Instruction Model) or Non-linear Pedagogy SAMPLE-PE curriculum.

Prior to the start of the training programme, coaches will be asked to design and deliver a coaching session to year 1 children, which will be video recorded by the research team. The video recordings of the session will subsequently be analyzed by two members of the research team with expertise in both pedagogical approaches. This exercise will enable the research team to determine whether each coach’s style of delivery is consistent with direct instruction-based teaching characteristics of Linear Pedagogy or more consistent with inquiry-based and problem-solving teaching characteristics of Non-linear Pedagogy. Coaches will then be allocated to either a Linear or Non-linear 5-week pedagogy training programme based upon their observed teaching style. This programme will comprise 3 h training each week delivered by the research team within a local primary school. Each training session will include a 90-min classroom theory session on either Linear or Non-linear Pedagogy, with pedagogical content knowledge relating to dance, gymnastics and ball sports, and a 90-min practical session of PE delivery to year 1 and 2 primary school children. The practical sessions will consist of a 45-min model lesson delivered in the pedagogical style by a member of the research team who has recognized expertise in PE teaching (Roberts et al., 2019b) followed by the coaches implementing their own lessons in accordance with the respective pedagogy.

All coaches will be provided with a scheme of work, lesson plans and a pedagogical framework for each PE subject (dance, gymnastics, and ball sports), a resource pack covering key elements of their respective pedagogical approach and copies of recorded theory and practical lessons were put online as coaches’ resources. A key aspect of the coaches training is the DIFFerentiation framework (see Table 1). Coaches will be trained on how they should utilize powerful teaching strategies of demonstration, instruction, and feedback in line with their respective pedagogies (linear or non-linear). This framework was based upon research from either a cognitive approach or ecological approach to motor learning. Coaches will be asked to complete a self-reflection either via diary or audio recording (Gibbs, 1988) each week concerning their implementation of the respective SAMPLE-PE pedagogy principles. This self-reflection will form the basis of discussions in weekly meetings with a member of the research team, alongside any changes necessary to the next week’s lesson plans. Coaches will also have the opportunity to access telephone support and a critical friend from the research team throughout the intervention delivery schedule.

**TABLE 1 T1:** DIFFerentiation framework used to support coaches teaching behaviors in the linear and non-linear pedagogy SAMPLE-PE curriculums.

	Linear pedagogy			Non-linear pedagogy	
	
General assumptions (‘DIFFerentitaion’)	Children in the autonomous and associative stage of learning	Children in the cognitive stage of learning	General assumptions (‘DIFFerentitaion’)	High motor competence children	Low motor competence children
	**(Fitts and Posner, 1973)**			**(Newell, 1986)**	

**Demonstration Isolated demonstrations of a motor skill by an adult or competent child is to be promoted as it offers a unique opportunity for learners to gather information about appropriate coordination patterns which could benefit performance.** (Shea et al., 1999)	Demonstration provided after practice of a task lead to stronger retention of learning than demonstration prior practice (Blandin et al., 1999)	Demonstration of a skill by an individual presenting high proficiency is beneficial for motor learning. (Blandin et al., 1999)	**Demonstration Adult demonstration is avoided as NLP encourages more than one optimal way to move in a functional manner.** (Williams and Hodges, 2005; Chow et al., 2016)	No demonstration is given as NLP suggests that it is more or less redundant as they are at the level where further demonstration will no longer provide them with useful information. (Chow et al., 2016)	A few highly competent children to demonstrate the movement in context so that the observing moderate to low competent children can see what they could do within their own movement. (Chow et al., 2016)

**Instruction The use of instruction should have both an internal (skill focus) and external focus of attention is allowed.** (Beilock et al., 2002; Wulf, 2007)	Verbal instructions should focus on movement outcomes rather than on the movements required by the task. (Beilock et al., 2002)	A skill focus instruction is encourage to support early acquisition of the skill as it has been found to be more effective in skill execution. (Beilock et al., 2002)	**Instruction The use of instruction is not encouraged if it is needed it should be short and not be prescriptive. Instead coaches were encouraged create games, scenarios and to manipulate task constraints to promote skills being learnt implicitly.**	Use of questioning and external focus as it allows children to problem solve toward a movement solution. (Chow et al., 2016) Coach use STEP framework to manipulate task constraints	If the child has no previous experience of the motor skill, the use of analogies can help as it chunks a large amount of information together that frees up mental capacity providing an external focus of attention. (Chow et al., 2016)

**Feedback and Frequency Feedback is a powerful tool in the coaches toolbox and should be used at the coaches discretion based on their judgment of a child’s motor competence. Feedback can either take the shape of knowledge of results or knowledge of performance.** (Sherwood, 1988; Sullivan et al., 2008)	Feedback should be provided only when error are large enough to warrant attention. (Sherwood, 1988)	Providing verbal feedback after each trial or as much as possible during early stages of acquisition is a priority (Sullivan et al., 2008) Practitioner should identify the component of the skills that needs to be learned, determine which is most critical for learning and prioritize feedback about the critical component of the task though this should not happen after every trial. (Weeks and Kordus, 1998)	**Feedback and Frequency Feedback should focus on children finding different movement solutions. Feedback is kept to a minimum and only used when children get stuck or to create instability in movement pattern.**	External feedback should only be given if they miss the mark. If they achieve the desired outcome, feedback is not necessary (Hodges and Franks, 2001)	Feedback should never be corrective. The coaches feedback should be minimal and if used should promote an external focus of attention. As with instructions analogies can be useful to support learning. Coaches can also utilize STEP framework to manipulate task constraints (Chow et al., 2016)

#### Linear Pedagogy

The SAMPLE-PE Linear Pedagogy intervention postulates that movement learning is a process that unfolds in identifiable linear phases (Schmidt, 2019). The Direct Instruction Model pedagogical approach will be used by coaches to create a PE environment where the learner first replicates the coaches’ technique, as well as scaffolding activities; starting with low environmental variability, as skill improves the learner will be placed into incrementally more variable and dynamic environments. To support the coaches’ learning design and delivery, they were trained to utilize three models: Fitts and Posner’s stages of learning (Fitts and Posner, 1973), Gentile’s taxonomy (Gentile, 2000) of movement skills, and the challenge point framework (Guadagnoli and Lee, 2004).

Coaches will be trained to identify children in each of Fitts’s and Posner’s three stages of learning (cognitive, associative or autonomous) and then, prior to the start of the PE lesson, to use this knowledge to modify lesson activities using Gentile’s taxonomy. The 16 categories of the taxonomy lead the coach through a logical sequence of potential progressions and force the coach to consider two main perspectives: the environmental context in which the skill takes place and the function that the movement skill must fulfill. Using Gentile’s taxonomy, a coach can manipulate the skill to its simplest form, in which the child has a stable base without any object manipulation and in an environment free from distraction. If the coach believes that a child or class of children have higher competence, they can use Gentilie’s taxonomy to create a skill context that is far more challenging, i.e., body in motion, manipulation of an object, and environmental factors dictating movement skill responses (Gentile, 2000). To support children’s individual needs during the lesson, coaches utilize the challenge point framework (Guadagnoli and Lee, 2004), which indicates that there is an optimal level of challenge for children to maximize learning in a given activity. Each lesson activity represents different challenges for children at different stages of learning a movement skill. The level of difficulty will be dependent upon a number of key variables: the skill level of the performer, the complexity of the activity, and the environment in which the activity is taking place. The more difficult the activity, the greater the learning potential, though this is related to an increase in task difficulty, and as such, the performance of the learner is expected to decrease. Thus, learning is maximized in PE when a child is optimally challenged. This framework supports coaches to critically assess if learning is taking place and consider how they can support a child to maximize learning.

The Linear Pedagogy curriculum was guided by four principles:

(1)There is a correct optimal movement pattern for each foundational movement skill. This is based on the idea that is there is a movement trace that acts as a reference of correctness to guide a child’s movement. The coach therefore relies heavily on demonstrations of an optimal movement pattern as this offers a unique opportunity for learners to gather information about appropriate coordination patterns and task requirements which can benefit performance (Sweeting and Rink, 1999; Hayes et al., 2008).(2)Movement skills are broken down or simplified into key components of a skill for learning, as performing an optimal movement pattern is often beyond the reach of children who are in the early stage of learning a skill.(3)Movement variability is viewed as noise in the system, which the child has to reduce in their quest toward mastery of a skill. The coach overcomes this by repetitive practice of the skills, which gradually reduces the amount of variability in the system, and the result is an efficient, reliable and accurate movement skill performance.(4)The focus of attention when performing a movement skill. The majority of research in this area highlights that promotion of an ‘external focus’ generally results in more effective performance and learning of a movement skill (Wulf, 2013). However, individuals in the cognitive phase of movement skill learning have been found to benefit from an internal focus of attention, e.g., a focus on the foot contact if dribbling a football (Beilock et al., 2002). Therefore, the SAMPLE-PE Linear Pedagogy curriculum coaches will be trained to create an internal focus of attention for children identified as in the cognitive phase of skill development (i.e., children with low movement competence), while for children progressing beyond this stage (i.e., children with higher movement competence), coaches focused on an external attention of focus.

The Linear Pedagogy PE curriculum was successfully trialed with year 1 children across three primary schools in summer 2016. A copy of the lesson plan can be found in Supplementary File 1.

